### Baseline eligibility assessment

Adherence will be measured electronically for 3 months prior to the first intervention to determine study eligibility and obtain a baseline, pre-intervention measure of medication adherence. The participant’s medication(s) and dosing schedule is determined by first reviewing the patient’s medical record and then confirming the medications with the patient. The study coordinator will record these data into the AdhereTech system. Participants will place their glaucoma medications inside AdhereTech electronic medication monitors that look like pill bottles. Patients will have different monitors for each of their glaucoma medications. Each time a bottle is opened, and the time and date are recorded. These records will be collected in real time and transmitted through the cellular data network so that adherence to medications can be calculated at any time interval (weekly, biweekly, monthly, etc.). The study coordinator will record each participant’s adherence data in the medical record during their study visits.

An adherent event is defined as taking medication within a specified time window of a dose on the previous day. For a once daily medication, an adherent event is defined as taking the medication within 24 ± 4 h of the previous day’s dose. For a twice daily medication, an adherent event is defined as taking the first medication dose within 24 ± 2 h of the previous day’s first dose and taking the second medication dose within 24 ± 2 h of the previous day’s second dose. For a three times daily medication, an adherent event is defined as taking the medication dose (first, second, or third) within 24 ± 1.3 h of the previous day’s corresponding medication dose (first, second, or third). For a four-time daily medication, an adherent event is defined as taking the medication dose (first, second, third, or fourth) within 24 ± 1 h of the previous day’s corresponding medication dose. The biological efficacy of medications dosed multiple times daily declines when not taken on time [38–40]. However, when calculating adherence for medications dosed more than once a day, we compare the current day’s doses to the previous day’s corresponding doses rather than simply the previous dose (second versus first, or third versus second) as lifestyle and sleeping patterns can result in medication times that are not equally spaced. This method of calculating adherence also allows for large shifts (time zone changes for work or vacation) or gradual changes in times when medications are taken without overly penalizing the patient, which can happen when calculating adherence relative to a median time. Additionally, this method of measuring adherence ensures that adherence credit is not given for instances where bottles are opened numerous times just prior to a clinic visit [119]. For participants on more than one medication, adherence will first be measured at the medication level and then aggregated to the person level by dividing the total number of doses of all medication(s) taken on time by the total number of doses of all medication(s) prescribed. Baseline adherence will be calculated monthly during the 3-month monitoring period. The median monthly adherence will be designated as the baseline adherence score; choosing the median will help to mitigate the effects of regression to the mean. We will exclude patients from participating in the study whose median baseline adherence score is > 80% on all of their glaucoma medications after a baseline observation period of 3 months.

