## Methods/design

In order to test the preliminary impact of the personalized eHealth intervention among non-adherent glaucoma patients, we will electronically monitor medication adherence longitudinally over 2 years. The two main components to be evaluated are (1) real-time automated adherence reminders using commercially available AdhereTech electronic medication monitors (AdhereTech, New York, USA) and (2) in-person tailored counseling with a medical assistant trained in MI (the eyeGuide program). Adherence will be monitored for all patients for a total of 2 years. Adherence will first be monitored for a 3-month period prior to the intervention to obtain baseline adherence and mitigate issues with regression to the mean and the Hawthorne effect [37]. Adherence will then be measured over a nine-month period of time during which the two interventions will be sequentially administered. Finally, adherence will be measured for 1 year after the conclusion of intervention to assess how well change in adherence is maintained over time.

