#### Sample size

We estimate that 46 participants will provide 80% power to detect at least a relative improvement of 15% in adherence (from an average pre- to post-intervention adherence rate of 0.7 to 0.8, and common standard deviation of 0.20) with a type-1 error rate of 5% and assuming a mild correlation of 0.3 between pre- and post-intervention adherences. We wanted adequate power to identify even a small effect size to evaluate whether this novel clinic-based intervention has any initial impact on adherence. This power calculation is based on the study by Okeke et al. in which patients < 75% adherent (measured with electronic monitors) were randomized to a standard counseling intervention vs. regular care [88]. This study demonstrated a 19% ± 20% improvement in adherence in the intervention group. We will aim to enroll 57 patients to allow for a 20% dropout rate; we anticipate this dropout rate given that we are targeting participants who are non-adherent to their recommended medication treatments. We aim to enroll 15 African-American patients to ensure that 25% of our patient population is African-American.

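### One run-in score both selects the non-adherent patients and serves as their baseline, so baseline-to-later comparisons are biased upward by regression to the mean

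*Protocol article*

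**What the plan says.** Under Baseline eligibility assessment, the protocol article gives the 3-month electronic monitoring period two jobs: "to determine study eligibility and obtain a baseline, pre-intervention measure of medication adherence". The same section defines the score: "The median monthly adherence will be designated as the baseline adherence score". It then excludes patients "whose median baseline adherence score is > 80% on all of their glaucoma medications".

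The protocol is aware of regression to the mean. Methods/design says that the run-in is there to "mitigate issues with regression to the mean and the Hawthorne effect", and Baseline eligibility assessment adds that "choosing the median will help to mitigate the effects of regression to the mean". Data analysis replaces the median with the third month if a significant Hawthorne effect is found. It concedes that this could expose the study to regression to the mean, but expects outlying months to fall at random across the run-in.

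Data analysis compares baseline with post-intervention adherence by paired t tests, for all pairs of periods. Sample size plans 46 evaluable patients to detect a rise from 0.7 to 0.8, "assuming a mild correlation of 0.3 between pre- and post-intervention adherences". The Discussion names the missing control arm as the largest limitation, but does not connect it with the selection at 80%.

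**The concern.** A patient enters because a score that varies over time fell at or below a cut-off. Some of those patients were in a poor spell that would have passed anyway. Measuring change from that same score counts their natural recovery as benefit, and no control arm shows how much recovery to expect.

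The reassurance that outlying months are random does not help. Random deviations followed by a one-sided cut-off are exactly what creates the bias.

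At stake are the comparisons of baseline with the reminder period, the counselling period and follow-up. The Discussion intends these data to show whether an effect is plausible before a randomized trial, so an artefact that is a sizeable share of the target could mislead that decision.

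**Working it through.** **1. The plan's own figure.** From Sample size: difference 0.10, common SD 0.20, correlation 0.3, 5% error (taken as two-sided), 80% power. SD of the difference = 0.20 × √(2 × (1 − 0.3)) = 0.2366. The noncentral t gives n = 46 with power 0.801, so the stated 46 is reproduced.

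**2. Null gain on the plan's own inputs.** With equal SDs, the slope of post on pre equals the correlation, 0.3, and selection on the pre value does not change that slope. With no intervention effect:

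expected gain = (1 − 0.3) × (mean of all monitored − mean of enrolled) = 0.7 × (M − 0.70).

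M, the mean of everyone monitored, is not in the document and is assumed here.

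| M (assumed) | Null gain, points | Chance of p < 0.05, n = 46 |
|---|---|---|
| 72.5% | 1.75 | 8% |
| 75% | 3.5 | 17% |
| 80% | 7.0 | 50% |
| 84.3% | 10.0 | 80% |

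**3. Truncated-normal check.** Gain = (1 − r) × (M − E[X | X ≤ 0.80]). With M = 0.70 and SD 0.20, the enrolled mean is 0.598. The gain is 0.7 × 0.102 = 0.071 at r = 0.3 and 0.5 × 0.102 = 0.051 at r = 0.5. For M from 60% to 80%, the range is 4.0-11.2 points at r = 0.3 and 0.6-1.6 points at r = 0.9.

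**4. What the median and the month-3 baseline achieve.** Simulation with no intervention effect, M = 70-75%, monthly SD 0.20, and monthly deviations independent within a person. Entries are null gains in points.

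| Month-to-month correlation | Single month selects and is baseline | Median selects and is baseline | Median selects, month 3 is baseline |
|---|---|---|---|
| 0.3 | 7.1-9.1 | 3.5-4.9 | 2.6-3.6 |
| 0.5 | 5.1-6.5 | 2.4-3.3 | 1.8-2.5 |
| 0.7 | 3.0-3.9 | 1.4-1.9 | 1.1-1.4 |
| 0.9 | 1.0-1.3 | 0.5-0.6 | 0.3-0.4 |

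The median about halves the artefact. The month-3 baseline trims it further but leaves most of what remains.

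**5. Spells that last a whole quarter.** Assumed SDs: person 0.13, quarter 0.13, month 0.08. The correlation among the enrolled is then 0.32-0.36, close to the planned 0.3. For M = 65-75%, the null gain is 3.9-6.6 points and the paired t test rejects in 28-68% of trials at n = 46. Two variations:

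- M = 50-60%, same SDs: 1.3-2.8 points, 7-17% rejection.
- M = 65-75%, more stable adherence (person SD 0.17, quarter SD 0.08): 1.8-3.0 points, 15-35% rejection.

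**6. Do the remedies work?** Under the SDs first given in step 5, with no intervention effect:

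- Regressing post on run-in score and evaluating at the mean of all monitored patients: 0.0-0.1 points.
- Mixed model on all monitored patients, period factor, random intercept only: 2.7-4.9 points remain.
- The same model with a person-level random period effect: about zero (−0.1 to 0.2 points).
- Selecting on months 1-2 with a month-3 baseline: 4.3 of 5.0 points remain at M = 70%. With independent monthly deviations, as in step 4, it leaves about zero.

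**The case against.** The protocol names the problem, uses three months rather than one, and takes a median. Step 4 shows that this helps, so a reader who infers that the quoted sentence is false goes too far: it promises help, not removal. It is insufficient rather than wrong.

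A reader might also infer that the primary outcome as a whole is contaminated. It is not. The plan compares all pairs of periods, and reminders against counselling, for example, does not use the selected score.

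A third tempting inference is that a significant gain is likely whatever the intervention does. The document does not support that, for four reasons:

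- The monitored mean is not given. Pre-screening by two self-report methods (Participants) could lower it and weaken the truncation.
- The correlation of 0.3 is a planning assumption that spans an intervention. Varied response to treatment would also lower it, so it is not evidence that adherence is unstable.
- The step 5 simulations for M = 65-75% that give 3.9-6.6 points have an enrolled mean of 0.58-0.63 and SD of 0.125-0.144, not the planned 0.70 and 0.20.
- Early Hawthorne inflation raises the run-in score and works in the opposite direction. Its size is unknown.

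Finally, this is an uncontrolled pilot that says so. That bears on how serious the point is. It does not remove the bias, because the study powers a formal test of change from baseline.

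**Conclusion.** The point holds for comparisons that use the run-in baseline. One window supplies both the filter at 80% and the pre value, so an upward change is expected under no effect whenever adherence is less than perfectly stable. Neither the median nor the conditional month-3 baseline removes it.

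The document does not fix the size. It runs from under 1 point, if adherence is very stable, to about the whole 10-point target. Roughly 4 to 7 points with 28-68% false rejection holds only for a monitored mean of 65-75% and a correlation among the enrolled near 0.3, before any Hawthorne offset. For a pilot meant to inform a randomized trial, this should be fixed; it does not invalidate the study.

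**What to change.** 1. Keep the run-in monitor data of everyone monitored, including those excluded for scoring above 80%. Consent and monitoring start at the first visit (Timeline), so the data exist.
2. Estimate the baseline-to-intervention change in one of two ways. Either regress the post score on the run-in score and evaluate the change at the mean of all monitored patients, or fit a mixed model to all monitored patients with a period factor and a person-level random period effect (or unstructured covariance across periods). State the covariance in the plan, because a random intercept alone is not enough.
3. Report the baseline paired t tests as descriptive.
4. Reword Baseline eligibility assessment to say that the median only partly reduces regression to the mean, and name the remaining bias beside the missing control arm in the Discussion.
5. If eligibility can still be changed, selecting on months 1-2 and taking month 3 as baseline is a partial remedy. It is complete only if monthly deviations are independent.

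Steps 1 to 4 cost analysis wording and data retention, with no new measurements. The downside is that the model extrapolates linearly to patients above 80% who are never treated, on a bounded scale. Its uncertainty is wider, and the headline gain will be smaller.

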### Timeline

The glaucoma counselor will meet with the participants in-person for seven study visits (Fig. 3). Intraocular pressure (IOP) will be measured at each study visit. The first study visit will include obtaining written informed consent, taking a 60-min survey and being instructed on how to use the AdhereTech electronic medication monitors. Three months later, during the second study visit, participants will be notified of their eligibility to continue in the study.

**Fig. 3 Fig3:**
[figure not shown]
Pilot study timeline

Eligible patients will participate in five more study visits. At the third study visit, 6 months from enrollment, participants will have their first 60-min eyeGuide counseling session with the glaucoma counselor and will take a 30-min survey. Their eye drop instillation will also be video-recorded. At the fourth study visit, 8 months from enrollment, participants will have their second 30-min eyeGuide counseling session and will take a 10-min survey. At their fifth study visit, 10 months from enrollment, they will have their final 30 min eyeGuide counseling session and have their eye drop instillation technique video-recorded. The intervention will end at the sixth study visit, 12 months from enrollment, where participants will come in to take a 45-min survey and undergo a 30-min semi-structured interview to obtain qualitative feedback about the eyeGuide program. Between the in-person eyeGuide counseling sessions, the glaucoma counselor will check-in with participants by telephone to update them on their adherence and discuss any issues they are having. These check-ins will take place more frequently at the beginning of the eyeGuide intervention, at 2 week intervals, and less frequently toward the end of the eyeGuide intervention (at 1 month intervals; Fig. 3). Participants will continue using their electronic medication monitors for an additional 12 months after the intervention has ended. At the seventh and final study visit, 24 months from enrollment, participants will return their electronic medication monitors and take a 45-min survey. Participants will receive a $35 stipend for each of their seven study visits and $35 for returning their adherence monitors.

### Personalized intervention tested in a pre-post design

#### Component 1

Participants will decide on a daily time when they would like to receive an automated reminder to take each dose of all of their glaucoma medications *if* they have not yet taken the dose. The reminder will be either an automated phone call or text message. Participants can also choose to activate an audio or visual alert [41–43]. AdhereTech will provide all of the preferred automated alerts. Participants’ adherence will be monitored throughout the 3-month period of receiving these automated reminders.

#### Component 2

After 3 months of receiving the automated reminders, participants will begin the tailored eyeGuide program. The program is tailored using computer programming so that the information each participant receives is personalized to their demographics and circumstances. The eyeGuide is tailored on the following variables: name, gender, race/ethnicity, ophthalmologist’s name, ophthalmologist’s gender, glaucoma type, past glaucoma surgeries or lasers, optic nerve photographs, visual field test results, use of the internet and/or smartphone, family support for eye drop instillation, and barriers to optimal glaucoma medication adherence.

Using the eyeGuide tablet-based tool, the glaucoma counselor will teach eye drop instillation, provide education tailored to a participant’s test results, elicit the barriers the participants face in managing their glaucoma, share tailored patient testimonials about strategies other patients used to overcome similar barriers, and brainstorm solutions together during the three in-person counseling sessions. The counselor will collaborate with participants to form an “action plan”—a short-term plan of steps to use to address identified barriers including how to integrate glaucoma medications into daily life (Fig. 2) [44–46]. The counselor will call participants once every 2 weeks between the first two eyeGuide study visits and then once monthly to provide feedback on their adherence level, check-in on their action plan, and help the participant identify new action steps. In-person counseling sessions will take place in a small Wi-Fi-enabled conference room at the Kellogg Eye Center located nearby an examination room where IOP measurement is taken.

Participants will receive 170 min of counseling (one 60-min counseling session, two 30-min counseling sessions, and five 10-min telephone calls), within the range of counseling time (106 ± 92.4 min) that achieved significant results in a meta-analysis of motivational interviewing [46]. The glaucoma counselor will also update the participant’s ophthalmologist on their adherence and action plan. Participants can call the counselor if questions arise during the intervention.

### Glaucoma-specific brief MI training program development

An ophthalmic technician will be trained as a glaucoma counselor through a glaucoma-specific brief MI training program that the study team has developed. The glaucoma-specific brief MI training program was developed by two behavioral psychologists and a psychotherapist trained through the Motivational Interviewing Network of Trainers [47]. The training program includes 16 h of didactic group training and 2 h of individualized coaching sessions. During the first training session, the prospective counselor learns about the following components of brief-MI-based conversation: reflective listening, asking open-ended questions, using affirmations, using elicit-provide-elicit technique to teach eye drop instillation, and summarizing [32]. The elicit-provide-elicit technique includes assessing the patient’s knowledge prior to giving information, asking permission to give new information, and then following up by eliciting patients’ response to the new information to evaluate their understanding.

The second training session focuses on learning how to problem-solve issues that may arise in patient encounters and learning how to make complex reflections. A reflection is a statement that paraphrases what the patient said to demonstrate active listening; a complex reflection is a statement that paraphrases and adds significant meaning. Prospective counselors also learn how to identify and promote change talk and develop an action plan to improve medication adherence. A video collection of glaucoma patients explaining their reasons for discontinuing their glaucoma medications is used for role playing during the training. Each session includes both didactic presentations and role playing (Table 1).

**Table 1 Tab1:** Glaucoma-specific brief motivational interviewing training curriculum

	Training session 1	Training session 2
Knowledge review	Presentation using “Elicit-Provide-Elicit”: “Motivational Interviewing Basics”	Review using E-P-E: “Skills learned in session 1”
		Skill review: “Quiz open vs. closed questions”
Skills/knowledge development	Paired activity: “A Taste of MI”	Group activity: “Health and Safety Quiz”
	Didactic using E-P-E: “What is reflective listening”	Triad activity: “Ambivalence”
	Paired activity: “Non verbal listening practice”	Didactic using E-P-E: “MI Spirit”
	Paired activity: “Hypothesis testing”	Didactic using E-P-E: “Simple vs. complex reflections”
	Paired activity: “Forming reflections”	Individual activity: “Reflective responses to sentence stems—three levels”
	Individual activity: “Forming reflections with sentence stems”	Paired activity: “Reflection practice”
	Group activity: “Forming reflections to glaucoma patient video examples”	Didactic using E-P-E: “Affirmations”
	Didactic using E-P-E: “Open ended questions”	Paired activity: “Making affirmations”
	Paired activity: “Asking open-ended questions”	Didactic using E-P-E: “Making summaries”
	Didactic using E-P-E: “Elicit-provide-elicit”	Paired activity: “Making summaries”
	Paired activity: “Teaching eye drop instillation with elicit-provide-elicit”	Didactic using E-P-E: “Eliciting change talk”
	Didactic using E-P-E: “Summarizing:	Paired activity: “Using elicit-provide-elicit to teach eye drop instillation”
	Paired activity: “Making summaries”	Didactic using E-P-E: “Importance Ruler”
	Paired activity: “Doing a full patient encounter using the MI skills learned”	Didactic using E-P-E: “Exploring goals and values”
		Paired activity” “Exploring goals and values”
		Didactic using E-P-E: “Confidence Ruler”
		Didactic using E-P-E: “Exploring strengths”
		Paired activity: “Rulers and strengths”
		Didactic using E-P-E: “Change Talk vs. Sustain Talk”
		Didactic using E-P-E: “Action Planning”
		Paired activity: “Putting it all together”
Skills Demonstration	Role playing: “Reflective listening”	Video demonstration: “Making Affirmations”
	Role playing: “Patient encounter using MI”	Video demonstration: “Making summaries”
		Video demonstration: “Elicit-Provide-Elicit for Change Talk”
		Video demonstration: “Exploring goals and values”
		Role play: “Rolling with resistance”
Skills self-reflection	Debrief: “What was learned?”	Debrief: “How will you implement this in clinic”

To ensure fidelity to MI training, the glaucoma counselor will practice delivering the intervention with at least five volunteer patients. S/he will be audio-recorded, and feedback will be provided prior to beginning the study. Competence in MI will be met before study visits are conducted. All study visit counseling sessions will be audio- recorded, and a random sample of sessions will be graded with a validated coding system tailored to the study, the One-Pass coding system [48] (Additional file 2**,** Glaucoma-specific one-pass). In addition to the initial training, the counselor will receive feedback on the graded sessions during booster training sessions over the course of the intervention [49]. The protocol for the eyeGuide intervention meets the Template for Intervention Description and Replication (TiDieR) standards [50].

